**Enrollment**							
	Eligibility screen	X					
	Informed consent	X					
Interventions: Elective PART			—^a^				
**Assessments**							
	Clinical examination	X		X	X	X	X
	Laboratory analysis^b^	X		X	X	X	X
	Registration of pretreatment gastrointestinal and genitourinary morbidities^b^	X					
	Registration quality of life using validated questionnaires	X		X	X	X	X
	Registration of PART-induced toxicity (Common Toxicity Criteria for adverse events)^b^		X	X	X	X	X
	Imaging (after discussion at an interdisciplinary tumor board)	X			X^c^	X^c^	X^c^

^a^Elective PART occurs during the whole period—daily instead of weekly, including the last day.

^b^Standard examinations; laboratory analysis is described in the protocol.

^c^In case of prostate-specific antigen relapse or symptoms.

### Secondary Endpoints

Secondary endpoints are quality of life (QoL), treatment-related acute and late toxicity, time to palliative ADT, time to castration-refractory prostate cancer (CRPC), CSS, and in-field pelvic and para-aortic disease control.

The QoL is measured using the European Organization for Research and Treatment of Cancer (EORTC) core questionnaire [41]. In addition, the EORTC prostate cancer module [42], the EuroQol 5 dimensions questionnaire [43], the International Consultation on Incontinence Short Form score [44], and the International Index of Erectile Function scoring system [45] are used to assess urinary, bowel, and sexual functioning and symptoms and evaluate the side effects of hormonal treatment associated with radiotherapy. QoL questionnaires are handed over to patients before treatment (baseline score) and at well-defined time points (end of treatment; 1 month, 3 months, 6 months, and 9 months after treatment; every 6 months until 5 years after treatment; and every 12 months until 10 years after treatment). QoL results will be presented in accordance with guidelines for reporting health-related QoL outcomes in cancer clinical trials published by the EORTC [46].

Treatment-related toxicity is assessed using the Common Toxicity Criteria for adverse events version 4.0 (CTCAE v4.0) [47]. Abdominal pain, diarrhea, enterocolitis, fecal incontinence, flatulence, hemorrhoids, proctitis, rectal fistula, rectal hemorrhage, rectal pain, noninfectious cystitis, hematuria, urinary frequency, urinary incontinence, urinary retention, urinary tract pain, erectile dysfunction, and fatigue are scored as adverse events according to CTCAE v4.0. Symptoms are scored before treatment. In addition, PART-induced acute toxicity (CTCAE v4.0) is scored weekly during radiation treatment and 1 month and 3 months after treatment. Furthermore, treatment-induced late toxicity (CTCAE v4.0) is scored at 6, 9, and 12 months after treatment; every 6 months until 5 years after treatment; and every 12 months until 10 years after treatment.

Time to palliative ADT is defined as the secondary endpoint of this trial. Indications to initiate palliative ADT are based on the EAU guidelines [39,40] and include the following: PSA>50 µg/L or PSA doubling time <6 months or symptoms due to progressive disease. In case of oligometastatic recurrence (1-3 synchronous metastases), metastasis-directed therapy is the preferential treatment option [48]. Time to CRPC is defined according to the criteria defined in the EAU guidelines [39,40]. CSS is defined as the interval from the date of diagnosis to the date of death from PCa or to the last follow-up date for censoring purposes, if the patient is alive and is still being followed at the time of data cut-off.

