### Radiotherapy: Structure Delineation, Planning and Delivery

#### Structure Delineation

Details on delineation of the clinical target volume (CTV) of the pelvic nodal areas are provided elsewhere [29]. Briefly, the elective LN areas consisted of the obturator, internal and external iliac, presacral, and common iliac nodes [16]. Concerning the prostate bed (postoperative setting) and the prostate (primary setting), both T2-weighted magnetic resonance imaging (MRI) and computed tomography (CT) images are used to optimize delineation, as detailed elsewhere [30-32].

Delineation of the PALN starts caudally at the level where the abdominal aorta splits into both common iliac branches and stops cranially at the level of the renal artery and vein. The CTV of the PALN is created by adding a 7-mm 3-dimensional expansion to the abdominal aorta and inferior caval vein, excluding intestinal loops and vertebral bodies. Unless kidney function is impaired, CT imaging is done using intravenous contrast to optimize the visualization of the vessels and improve discrimination with the intestinal loops. The use of oral contrast to better visualize these intestinal loops is left at the discretion of the treating physician. Details concerning protocols on bladder filling and rectal preparation are provided elsewhere [33]. The planned target volume (PTV) of the LNs is created by expanding the CTV with an isotropic margin of 7 mm.

Concerning the organs at risk (OARs), the following structures are delineated: bladder, anal canal, rectum, sigmoid colon, small intestine, large bowel, femoral heads, spinal cord, cauda equine, bone marrow, and kidneys. Figure 2 depicts the delineation of the OARs.

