### Laboratory Analysis

All laboratory tests are considered standard and include PSA measurement, peripheral blood cell count with formula, kidney function tests, liver function tests, and testosterone measurement. These laboratory tests are done during every follow-up visit.

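### The CTCAE terms stated to be scored include none for kidney, blood, nerve or nausea/vomiting, so low-grade harm from the added para-aortic field has no stated route into the toxicity endpoint

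*Protocol article*

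**What the plan says.** The Secondary Endpoints section makes "treatment-related acute and late toxicity" a secondary endpoint, assessed with CTCAE v4.0. It then names the terms. The first part of the list is "Abdominal pain, diarrhea, enterocolitis, fecal incontinence, flatulence, hemorrhoids, proctitis, rectal fistula, rectal hemorrhage, rectal pain, noninfectious cystitis, hematuria". The rest reads "urinary frequency, urinary incontinence, urinary retention, urinary tract pain, erectile dysfunction, and fatigue are scored as adverse events according to CTCAE v4.0". A pretreatment score is also planned. Acute toxicity is scored weekly during radiotherapy and at 1 and 3 months, and late toxicity from 6 months up to 10 years. Under Sample Size and Statistics, acute and late toxicity will be summarized as incidence and as Kaplan-Meier risk estimates.

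The Structure Delineation section describes the added volume. It starts at the aortic bifurcation and "stops cranially at the level of the renal artery and vein". The organs at risk to be contoured include "small intestine, large bowel, femoral heads, spinal cord, cauda equine, bone marrow, and kidneys".

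The Laboratory Analysis section lists PSA together with "peripheral blood cell count with formula, kidney function tests, liver function tests, and testosterone measurement", and adds: "These laboratory tests are done during every follow-up visit". Table 1 also marks laboratory analysis at screening and on the last day of treatment; the weekly on-treatment cell is blank.

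The Safety section requires immediate reporting to the sponsor of serious adverse events, given there as grade 3 or higher, and withdraws patients from para-aortic treatment at grade 4 toxicity. Neither rule is limited to the listed terms.

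**The concern.** What is new in this trial is the para-aortic field; the historical controls also received pelvic radiotherapy with ADT. The scored list is weighted towards rectal, urinary and sexual effects. Three organs that the protocol itself treats as at risk (kidneys, bone marrow, spinal cord) have no matching term, and neither do nausea and vomiting.

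The Introduction says that, to the authors' knowledge, this strategy has never been evaluated in prostate cancer. The Safety section draws its expectation about grade 4 toxicity from cervical cancer. The Discussion hopes that the results will support a randomized phase III trial and speaks of keeping toxicity acceptable. Toxicity estimates built only on the listed terms would describe the pelvic component better than the component under test.

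**Working it through.** No formula is needed for the main point. The check is to classify the listed terms, set them beside the organs at risk, and look for any other route by which the missing harms could be graded.

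**Step 1: classify the terms (Secondary Endpoints).**
- Gastrointestinal, 10: abdominal pain, diarrhea, enterocolitis, fecal incontinence, flatulence, hemorrhoids, proctitis, rectal fistula, rectal hemorrhage, rectal pain.
- Urinary, 6: noninfectious cystitis, hematuria, frequency, incontinence, retention, urinary tract pain.
- Erectile dysfunction, 1. Fatigue, 1.
- Total: 10 + 6 + 1 + 1 = 18.

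**Step 2: compare with the harms at issue.**

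| Harm | Listed terms | Other stated route |
|---|---|---|
| Kidney function | 0 of 18 | Tests at screening, last day and each follow-up visit; not stated to be graded |
| Bone marrow/blood | 0 of 18 | Same as kidney |
| Spinal cord/nerve | 0 of 18 | None below grade 3 |
| Nausea/vomiting | 0 of 18 | None below grade 3 |
| Bowel in general | At least 3 (abdominal pain, diarrhea, enterocolitis) | Already scored |

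For all rows, serious events of grade 3 or higher go to the sponsor under the Safety section. That is expedited reporting. It is not scheduled scoring against a baseline, and it does not reach grades 1 and 2.

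**Step 3: baseline.** The pretreatment morbidity row of Table 1 covers gastrointestinal and genitourinary problems only. Baseline laboratory values exist, because Table 1 marks laboratory analysis at screening. No baseline is stated for nausea, vomiting or neurologic symptoms beyond the general statement that symptoms are scored before treatment.

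**Step 4: possible size.** The documents give no rate for the omitted events, so a range is assumed.
- Evaluable patients: planned 151 less 10% dropout = 151 × 0.90 = 135.9, about 136.
- At 2%: 136 × 0.02 = 2.7, about 3 patients.
- At 5%: 136 × 0.05 = 6.8, about 7 patients.
- At 10%: 136 × 0.10 = 13.6, about 14 patients.

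If the assumed rate covers events of any grade, some will be grade 3 or higher and may be reported separately. The counts are therefore upper bounds for the number left without a route at each assumed rate.

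**The case against.** **The list may not be exclusive.** The section opens by saying generally that toxicity is assessed with CTCAE, and neither the later sentences on timing nor Table 1 restricts the terms. This is fair, and the full case-report form may be longer. But the article sets out 18 named terms with no indication that they are examples. The footnote to Table 1 that refers to the protocol for detail does so for laboratory analysis, not for toxicity terms. The point is about an explicit list as written, and it falls away if the full protocol has a longer one.

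**Marrow and kidney data are collected.** This stands in large part. Blood counts and kidney tests are drawn at screening, at the end of treatment and at every follow-up visit, so grades can be derived and nothing collected is lost. Two gaps remain: the article does not say that these results are graded, and Table 1 marks no weekly laboratory test during treatment, although acute toxicity is scored weekly. Laboratory tests cannot record nausea, vomiting or myelopathy.

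**Stronger readings that the documents do not support.** A reader might infer that the list covers only pelvic, sexual and fatigue effects. It does not: abdominal pain, diarrhea and enterocolitis are not confined to the pelvis. A reader might infer that harms of the added field are never graded. The Safety rules for grade 3 or higher and for grade 4 contradict that. A reader might want gastric and duodenal terms added. Stomach and duodenum are not among the listed organs at risk, so the document gives no anchor for them. Finally, no passage makes toxicity the test for going on to phase III, and the only comparison with the historical controls that the article describes is of clinical relapse-free survival.

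**Conclusion.** The concern holds in a limited form. The terms stated to be scored omit four kinds of harm, and for three organs this sits badly with the protocol's own list of organs at risk. The gap concerns mainly grades 1 and 2. For kidney and marrow the data exist but their grading is unstated; for neurologic symptoms and nausea or vomiting there is no stated scoring at all.

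The effect would be to understate toxicity from the para-aortic component in the incidence and Kaplan-Meier summaries. The count of 0 in 18 rests on no assumption. The figure of roughly 3-14 patients rests on the assumed 2-10% rate and on about 136 evaluable patients, and it is an upper bound for those rates. The primary endpoint is not affected. The change should be made, because it is cheap and the added field is what the trial tests.

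**What to change.** Add to the scored CTCAE v4.0 terms in the Secondary Endpoints section:
- nausea and vomiting;
- anemia and decreased platelet, neutrophil and lymphocyte counts;
- creatinine increased;
- a myelopathy/neuropathy term.

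Score each before treatment as well as afterwards. State in the Laboratory Analysis section that the laboratory terms are CTCAE-graded from tests already drawn under that section and Table 1, and apply this retrospectively to enrolled patients. If the full protocol already scores these terms, it is enough to bring the published list into line with it.

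The cost is a few extra form lines at existing visits and no new test. Symptom terms will be incomplete for patients treated before the amendment, so reports should give the number of patients in whom each term was scored. Because Table 1 marks no weekly laboratory tests, derived blood-count and creatinine grades will not describe the treatment weeks themselves; the report should say so.

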### Hormonal Treatment

ADT will be started 2-4 weeks before the start of radiotherapy to overcome the androgen receptor-induced radioresistance [36]. The duration of ADT is 24 months (long term) as all patients belong to a very high-risk population and long-term ADT is the standard of care in these patients [37,38]. Of note, both the use of an luteinizing hormone-releasing hormone-analogue and an antagonist is allowed.

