### Sample Size and Statistics

We aim to improve 5-year cRFS by 15% (primary endpoint). This would result in a 5-year cRFS of 75% compared with the control group with WPRT only that reaches a 5-year cRFS of 60% [18,20]. For a log-rank test comparing two survival curves with a one-sided significance level of .1, assuming uniform accrual with an accrual time of 48 months and a follow-up time of 12 months, a sample size of 137 is required to obtain a power of at least 80%. Taking into account a dropout of 10%, we aim to include 151 patients. The control group consists of pN1 patients treated with adjuvant ADT and WPRT alone from whom the data have been published before [20]. The incidence of acute and late toxicity will be recorded. In addition, actuarial risk estimates for developing acute and late toxicity will be calculated using Kaplan-Meier analysis. Time to palliative ADT, time to CRPC, CSS, and in-field pelvic and para-aortic disease control will be calculated using Kaplan-Meier actuarial analysis. cRFS, time to CRPC, CSS, and in-field pelvic and para-aortic disease control times are defined from the date of LN dissection until an event or last follow-up. Statistical analysis will be performed using the latest version of SPSS (IBM Corp, Armonk, NY, USA).

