## Results

Ethical approval to conduct this study (version 2.0 from December 1, 2016) was granted by the Medical Ethics Committee University Hospitals/Catholic University Leuven (14/12/2016). Written informed consent of patients is mandatory before recruitment. Recruitment of patients started in 2017 and is expected to be completed by March 2020.

As a result of the PART trial, we will publish the 5-year cRFS, defined as the absence of any cR that would be visible at top of the line imaging, our primary endpoint. Furthermore, we will compare these results with the 5-year cRFS of a historical control group of patients who underwent WPRT; the results of this historical control group have already been published by Poelaert et al [20]. This control group includes patients with PCa who underwent PLND and pelvic radiotherapy between January 2000 and January 2016 at a tertiary center (GUH). Those patients were rigorously treated by several authors of this manuscript ([name], VF, [name], and NL). A total of 154 pN1 patients with PCa who received WPRT were included. As described in the “Sample size and Statistics” section, survival curves of both groups will be compared using log-rank test. Besides, acute toxicity and QoL results will be published after short-term follow-up, whereas treatment-related late toxicity and QoL results, time to palliative ADT, time to CRPC, CSS, and in-field pelvic and para-aortic disease control will be published after a longer follow-up period.

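### Cause-specific survival has two start dates, time to palliative ADT has none, and the pre-radiotherapy lead-in is not aligned with the historical controls

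*Protocol article*

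**What the plan says.** Two current sections of the protocol article define CSS. Secondary Endpoints: "CSS is defined as the interval from the date of diagnosis to the date of death from PCa". Sample Size and Statistics: "cRFS, time to CRPC, CSS, and in-field pelvic and para-aortic disease control times are defined from the date of LN dissection".

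The second list covers four endpoints: clinical relapse-free survival (cRFS, the primary endpoint), time to CRPC, CSS and in-field control. Time to palliative ADT is not among them. Secondary Endpoints gives the indications for starting palliative ADT and says "Time to palliative ADT is defined as the secondary endpoint of this trial", but gives no date from which the time runs.

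The exclusion criteria rule out patients whose PSA has risen after its postoperative nadir, patients with clinical M1 disease, and patients with nodal disease on planning imaging. The only timing given for the run-up to radiotherapy is in Hormonal Treatment: "ADT will be started 2-4 weeks before the start of radiotherapy". Nothing is said about the interval from dissection to radiotherapy.

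The controls are described in Results: "This control group includes patients with PCa who underwent PLND and pelvic radiotherapy between January 2000 and January 2016", and "A total of 154 pN1 patients with PCa who received WPRT were included". For the comparison, "survival curves of both groups will be compared using log-rank test".

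**The concern.** Diagnosis is made at biopsy and comes before dissection, so the two CSS definitions give two different curves from the same patients. An analyst could cite the protocol for either. For time to palliative ADT the analyst has to choose the origin unaided.

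The second issue touches the primary comparison. A patient joins the trial only after dissection, and only if no relapse has been detected by then. The months between dissection and radiotherapy are therefore free of detected relapse by selection, yet they count as cRFS time. In a randomised trial this interval would balance on average. Here PART patients come from several centres from 2017 onwards, and the controls from one centre over 2000-2016. If one group has the longer lead-in, its curve is lifted for a reason unrelated to para-aortic irradiation.

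**Working it through.** **1. CSS, side by side.** Secondary Endpoints: diagnosis to death from prostate cancer. Sample Size and Statistics: dissection to event or last follow-up. The starting dates differ, so the definitions conflict. No arithmetic is needed, and the article gives no figure for the interval between the two dates.

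**2. The plan's own figure.** The stated sample size is 137, for 75% against 60% cRFS at 5 years, one-sided .10, 80% power, 48 months' accrual and 12 months' follow-up.
- Hazard ratio under exponential survival: ln(0.75)/ln(0.60) = 0.563.
- Mean event probability over the two groups: 0.208.
- Schoenfeld: 55 events, 265 patients in total, 133 per group.
- Freedman: 58 events, 280 in total, 140 per group.
- Exponential-hazard formula: 277 in total, 139 per group.

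The 137 is reproduced to within 3% as the size of one group. Neither the CSS origin nor the lead-in enters it, so correcting the origins leaves it unchanged.

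**3. Effect of an unequal lead-in on 5-year cRFS.** Inputs: control cRFS of 60% at 5 years (Sample Size and Statistics) and, as assumptions, exponential survival, no treatment effect, and a lead-in g months longer in PART than in controls.
- Monthly hazard: -ln(0.60)/60 = 0.0085.
- Apparent 5-year cRFS in PART: 0.60^((60 - g)/60).
- g = 3: 0.60^(57/60) = 0.616, a gain of 1.6 points, or 10% of the 15-point target.
- g = 6: 0.60^(54/60) = 0.631, a gain of 3.1 points, or 21% of the target.

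If the controls had the longer lead-in, the same formula would lift their curve instead.

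**4. Effect on the log-rank test.** Simulation of 137 PART patients against 154 controls with the same hazard after the lead-in, uniform accrual over 48 months, the same follow-up pattern in both groups, one-sided .10, and 4000 runs per cell (simulation standard error at most 0.008).

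| Extra lead-in in PART | Minimum follow-up 12 months | Minimum follow-up 36 months |
|---|---|---|
| 0 months | .10 | .10 |
| 3 months | .19 | .17 |
| 6 months | .35 | .28 |
| 6 months in both groups | .11 | .10 |

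The 12-month column follows the sample-size assumptions. The 36-month column gives a median potential follow-up of 36 + 48/2 = 60 months, the point at which Time Schedule places the primary analysis.

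The last row matters most: an equal lead-in in both groups leaves the error essentially at its nominal level. Only a difference between groups does harm.

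**The case against.** The strongest reply is that the controls had to pass through the same gate. They too had a dissection and then received pelvic radiotherapy, so they also survived to treatment. Lead-in time common to both groups is not bias, as the last row of the table shows. This stands, and it limits the point to a possible mismatch.

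A reader might infer that the primary comparison is tilted towards PART, because consent, staging and multi-centre referral would lengthen the interval. The documents do not support that. Patients are recruited at the existing multidisciplinary consultation and in the radiation oncology departments, and nothing says that baseline imaging exceeds what the controls had. A longer interval among the 2000-2016 controls fits the text equally well and would work against PART.

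A reader might also infer that every endpoint runs from dissection. Only the four listed do; toxicity and quality of life after treatment are scheduled relative to treatment.

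Finally, dissection may have been chosen to match the origin in the published control series, which is not available here. That is possible, but the article does not say so. A shared dissection origin would still leave open whether the interval to radiotherapy is similar. None of this touches the conflicting CSS definitions or the missing origin for time to palliative ADT.

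**Conclusion.** The CSS contradiction is certain and rests on the text alone. So does the absence of a start date for time to palliative ADT. Both concern secondary endpoints, and no stated sample-size figure depends on them.

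The lead-in is a gap in the specification of the primary comparison and has not been shown to bias it. The article gives the dissection-to-radiotherapy interval for neither group, gives no time origin for the controls, and mentions no delayed entry. The 3- and 6-month differences are assumptions with no anchor in the document. The results also rest on exponential survival, equal follow-up patterns and no treatment effect. They show that a modest mismatch would matter at a one-sided .10 level; they do not estimate this trial's error rate.

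**What to change.** 1. Delete one of the two CSS definitions so that a single origin applies, and give time to palliative ADT the same origin.
2. For the comparison with the historical controls, state one origin for both groups. Either the start of radiotherapy, or dissection with left truncation (delayed entry) at the start of radiotherapy, removes the lead-in from the time at risk.
3. Report the distribution of the dissection-to-radiotherapy interval in each group.

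The cost is a wording change with no effect on the sample size. It does need radiotherapy start dates for the controls. A reader might assume that these are on file, but the article does not say so, and they should be confirmed before the analysis is fixed. Times counted from radiotherapy will be a few months shorter than those counted from surgery, which should be noted when comparing with published series. Because ADT begins before radiotherapy, the chosen origin should be named as a date and not as the start of treatment.
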